#### Power

The power analysis was performed for the primary outcome, the difference in the change in the relative distance to the median BMI-for-age, and takes into account the intraclass correlation among children within clinics [64].

Across the 49 selected medical centers (Figure 1), the number of children aged between 3 and 8 years with overweight or obesity ranged from 500 to 6000 per site, with a coefficient of variation of 0.9. On the basis of previous studies [65,66], we assumed that the participating children would average approximately 30% to 40% above the median (which equates to the 97th percentile; SD 20% to 25%). Based on an expected effect size of 5.3% (SD 14.7%), a Cohen *h* of approximately 0.3 was used.

With 24 clinics in the intervention arm and 26 in the control arm and assuming a 2-sided α of .05, an intraclass correlation of 0.01, a coefficient of variation of 0.9, and an SD of 27.0% for change in BMI distance, a sample size of approximately 3300 children per arm provides adequate power to detect a difference in difference (DID) of 1 to 5 units in the primary outcome.

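### On the Power section's own inputs, about 3300 children per arm gives adequate power only from about 3.5 units upward, not from 1 unit, and two SDs are left unreconciled

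*Protocol article*

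**What the plan says.** The Power section fixes every input that the calculation needs. The clinics: "With 24 clinics in the intervention arm and 26 in the control arm". The test: "assuming a 2-sided α of .05". The clustering and spread: "an intraclass correlation of 0.01", "a coefficient of variation of 0.9, and an SD of 27.0% for change in BMI distance". The conclusion is that about 3300 children per arm "provides adequate power to detect a difference in difference (DID) of 1 to 5 units in the primary outcome". No power percentage is given.

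The preceding paragraph of the same section introduces a second SD and a standardised effect: "Based on an expected effect size of 5.3% (SD 14.7%), a Cohen *h* of approximately 0.3 was used". It also gives an SD of 20% to 25% for how far participating children are expected to lie above the median.

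**The concern.** With one SD, one intraclass correlation, one coefficient of variation and one sample size, there is one detectable difference for each level of power. A fivefold range of differences, all said to be detected with adequate power, is credible only if the smallest of them is. A difference of 1 unit is 1/27 = 0.037 of the stated SD of change, which is very small for 50 clinics.

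What is at stake is how the trial's sensitivity is understood. The Discussion (Balancing Intensity and Feasibility) describes a lower-dose model of coaching, so effects below the expected 5.3 units are of real interest. A reader who trusts the stated range would think the trial well placed to detect 1 to 3 units when it would often miss them.

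The two SDs matter because the detectable difference is proportional to the SD: moving from 27.0% to 14.7% nearly halves it.

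**Working it through.** **Inputs, all from the Power section.** Clinics k1 = 24 and k2 = 26; n = 3300 children per arm; ICC = 0.01; CV of clinic size = 0.9; SD of change = 27; two-sided alpha = 0.05. Assumption: adequate means at least 80% power, since no figure is given; 90% is shown as well.

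**Design effect for unequal clusters.** DE = 1 + ((CV² + 1)·m − 1)·ICC, where m = n/k and CV² + 1 = 1.81.
- Intervention: m = 3300/24 = 137.5; DE = 1 + (1.81 × 137.5 − 1) × 0.01 = 3.479.
- Control: m = 3300/26 = 126.9; DE = 1 + (1.81 × 126.9 − 1) × 0.01 = 3.287.

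**Standard error.** SE = 27 × √(3.479/3300 + 3.287/3300) = 1.22 units.

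**Power** (noncentral t with 24 + 26 − 2 = 48 df; normal approximation Φ(δ/SE − 1.96) beside it):

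| DID (units) | t, 48 df | Normal |
|---|---|---|
| 1 | 12.6% | 12.7% |
| 2 | 36.1% | 37.3% |
| 3 | 67.2% | 68.9% |
| 3.5 | 80.1% | 81.7% |
| 4 | 89.4% | 90.5% |
| 5 | 98.0% | 98.3% |
| 5.3 | 98.9% | 99.1% |

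**Smallest detectable DID.** By the t method, 3.50 units at 80% power and 4.04 at 90%. By normal quantiles, 2.80 × 1.22 = 3.4 and 3.24 × 1.22 = 4.0.

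**Attempts to reproduce adequate power at 1 unit** (normal approximation, one change at a time from the stated inputs unless noted):
- 25 control clinics, the number in the Results text, instead of 26: 12.6%.
- Equal clinic sizes (CV = 0): 16.6%.
- Unlimited children in the same 50 clinics, CV 0.9: 16.2%.
- One-sided alpha: 20.4%.
- No clustering at all: 32.4%; 80% would need 11,444 children per arm.
- SD 14.7 with the stated clustering: 32.4%.
- SD 14.7 and no clustering: 78.9%; 80% needs 3393 per arm.

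Only the last comes close to 3300. It drops both the stated SD of 27 and the clustering that the section says it took into account. The article does not say how 3300 was obtained, so the match may be coincidence.

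**Standardised effects.** 5.3/14.7 = 0.36. 5.3/27 = 0.20. Neither is about 0.3.

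**If the SD of change were 14.7.** With the stated clustering, the detectable differences scale by 14.7/27: 3.50 × 14.7/27 = 1.9 units at 80% and 4.04 × 14.7/27 = 2.2 at 90%. Even then, 1 unit is out of reach.

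**The case against.** **The range may be only the set of effects examined.** No power percentage is attached to it, so it could be a span of scenarios. But the sentence claims adequate power across that span, and 13% meets no usual standard. This objection fails.

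**The trial is well powered for the effect it plans on.** This stands. Power is about 99% at 5.3 units, even with the larger SD, which is the conservative choice. A reader might infer that the sample size is inadequate or the design unsound; the article's figures do not support that. Nor does it follow that a null result would be misread as excluding small effects, since a reported confidence interval would show what is excluded.

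**Three SDs appear, and a reader might call all three conflicting.** The section does not support that. The 20% to 25% describes the spread of the level above the median and is not an SD of change. An SD of change may exceed it. With equal variances at both times, the correlation between baseline and follow-up is 1 − 27²/(2 × SD²), which is 0.09 for a level SD of 20 and 0.42 for 25. That is low enough to ask about, but it is not a contradiction. The open question is 14.7% against 27.0%, and there the fault is missing justification.

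**The effect-size label does not drive the result.** This also stands. The 3300 sentence is in units with SD 27; neither Cohen h nor 0.3 enters it. The label and the loose rounding are minor.

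**Precision under the actual analysis may differ.** A reader might add that propensity weighting makes power worse still. It may cost precision, but repeated measures and covariate adjustment may gain some. The article quantifies neither, so no net direction can be claimed.

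**Conclusion.** The claim of adequate power from 1 to 5 units is wrong as written below about 3.5 units. Under the stated inputs, power is about 13% at 1 unit, 36% at 2 and 67% at 3; it is about 98% at 5 units. No single change to the inputs among those tried brings 1 unit near 80%.

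This rests on reading adequate as 80% or more, on the usual design effect for unequal clusters, and on a coefficient of variation of 0.9 applying to the children analysed. The article gives that figure for all eligible children per site.

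Separately, 14.7% and 27.0% are left unreconciled, and the quoted standardised effect of about 0.3 matches neither. Because the outcome is a continuous change, the measure should be Cohen d. These are smaller matters. The main defect is an overstated sensitivity; power for the expected effect is not in doubt.

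**What to change.** Remove the 1-to-5-unit range. State instead that, with SD of change 27, intraclass correlation 0.01, coefficient of variation 0.9, 24 and 26 clinics and two-sided alpha 0.05, about 3300 children per arm gives 80% power for a DID of about 3.5 units and 90% for about 4.0 units (noncentral t, 48 df; 3.4 and 4.0 by the normal approximation). Name the method and use it throughout.

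State which SD of change applies and why, and recompute these figures if it is not 27. Replace the Cohen h of about 0.3 with Cohen d for the chosen SD: 0.36 for 14.7%, or 0.20 for 27.0%.

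The cost is a reworded passage in the Power section and a less favourable stated sensitivity. Sample size, recruitment and analysis do not change. Results are expected in spring 2027, so the correction can be made before they are reported.

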#### Planned Statistical Analysis

To evaluate the intervention effect, we will use a DID approach comparing the change in BMI-for-age distance between the WC4K and usual care groups. Using repeated measurement data, the DID model will estimate the average within-child change from baseline to follow-up, using all available BMI data points.

A linear mixed-effects regression model will be used to account for clustering. The model will include a random intercept for “child” to account for repeated measures. Baseline covariates with standardized mean differences (SMDs) greater than 0.1 between groups will be included as fixed effects, along with relevant demographic, clinical, and site-level characteristics.

For descriptive comparisons, SMDs will be used to assess the balance between groups.

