#### WC4K Lifestyle Coaching

Health coaching was delivered by a centralized team of MI-trained coaches with more than 5 years of experience. Coaching included a 45-minute intake session and 5 to 9 follow-up sessions (approximately 20 min each) over 24 months.

Coaches worked with parents to set goals, track progress, and reinforce behavior change. Children were encouraged to attend the coaching sessions, but participation was optional and dependent on family preferences and logistics.

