#### Outcome Measures

The primary outcome is a change in BMI-for-age over 24 months, measured as the relative distance from the median using EMR data and CDC extended BMI percentiles [50,60-62]. No additional visits were scheduled for height and weight collection. Secondary outcomes include parent-reported behavior changes.

At KPSC, height and weight are measured by clinical staff during routine care and automatically recorded in the EMR, allowing for real-time BMI calculation (weight in kg divided by height in m^2^).

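### The primary outcome is change over 24 months, but the stated model estimate is an average baseline-to-follow-up change with no time point, so as written it depends on visit timing

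*Protocol article*

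**What the plan says.** The Outcome Measures section of the protocol article states: "The primary outcome is a change in BMI-for-age over 24 months". The values come from the electronic medical record, and "No additional visits were scheduled for height and weight collection".

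The Planned Statistical Analysis section then names the quantity to be estimated: "the DID model will estimate the average within-child change from baseline to follow-up, using all available BMI data points". On structure it adds: "The model will include a random intercept for “child” to account for repeated measures". It mentions no time since baseline, no visit window, no 24-month contrast and no latest date for an eligible BMI value.

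Two other sections bear on this. Under WC4K Lifestyle Coaching: "Coaching included a 45-minute intake session and 5 to 9 follow-up sessions (approximately 20 min each) over 24 months". The Power section gives an expected effect of 5.3% and attaches no time point to it.

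**The concern.** The outcome has a 24-month horizon, while the estimate has none. If every post-baseline BMI value enters as one follow-up level, a value taken a few months after referral counts in the same way as one taken at two years. The result is an average of the effect over whatever times children happened to be measured.

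Two things are at stake. First, the reported effect may not be the 24-month change that defines the primary outcome. Coaching is spread over the same 24 months, so early values reflect partial exposure. Second, a baseline-versus-follow-up comparison without time since baseline has no protection if the arms are measured at different times. A BMI trend common to both arms would then appear as a treatment difference.

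**Working it through.** **Step 1. The two statements side by side.** The outcome is a change over 24 months, from routine measurements. The estimate is an average change from baseline to follow-up, from all available values. Only the first names a time.

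**Step 2. The plan's own figure.** The article gives no figure for the 24-month effect as against a follow-up average, so there is none to reproduce. The 5.3 units from the Power section serve below only as a scale. Treating them as the 24-month value is an assumption.

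**Step 3. What a pooled estimate returns.** Let f(t) be the effect at month t divided by the effect at month 24. If all children are seen at months t1 to tk, the arm-by-post term of a child-intercept model estimates the 24-month effect multiplied by

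A = (1/k) × Σ f(tj).

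With linear build-up, f(t) = t/24:

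- visits at 12 and 24: (0.5 + 1)/2 = 0.75, so 5.3 becomes 3.97;
- visits at 6, 12, 18 and 24: (0.25 + 0.5 + 0.75 + 1)/4 = 0.625, so 5.3 becomes 3.31;
- a visit at 24 only: 1.00.

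Other shapes, with A in the cells (schedules and shapes are all assumed):

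| Shape of effect | 12/24 | 6/12/18/24 | 3/6/9/12/24 |
|---|---|---|---|
| Linear to month 24 | 0.75 | 0.625 | 0.45 |
| Full by month 12 | 1.00 | 0.875 | 0.70 |
| Full by month 6 | 1.00 | 1.00 | 0.90 |
| Peak at 12, half lost by 24 | 1.50 | 1.375 | 1.20 |

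The direction of the discrepancy therefore depends on the shape.

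**Step 4. Check by simulation.** The assumptions were 1500 children per arm, a between-child SD of 20, a within-child SD of 10, a true effect of −5.3 at 24 months built linearly, and the mean of four replicates. The pooled estimate was −3.88 (visits at 12/24), −3.10 (6/12/18/24) and −5.26 (24 only). For four visits the simulation error is √(2 × 10² × 1.25/1500)/√4 = 0.20, so −3.10 agrees with the expected −3.31. A model with linear time and an arm-by-time term, evaluated at 24 months, gave −5.31, −4.91 and −5.26 on the same schedules.

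**Step 5. Unequal timing.** Assume no treatment effect, a common drift of +4 units over 24 months, visits at 6/12/18/24 in the intervention arm and visits at 12/24 in the control arm. The expected spurious difference is 4 × (0.625 − 0.75) = −0.50 units. The simulated pooled value was −0.68 (simulation error about 0.2), against −0.03 for the model with time.

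**Step 6. No upper limit.** Enrollment began in fall 2022, recruitment in intervention clinics ended in December 2024, and results are due in spring 2027. The first children pass 24 months in fall 2024, more than two years before results. The last reach it in December 2026. Taken literally, using every available value gives early entrants follow-up past 24 months that late entrants cannot have.

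**The case against.** The strongest reply is that the pooling is read into the text. The analysis section speaks of repeated measurements and does not exclude a time term. The average may mean an average over children, not over visits. Change over 24 months may simply name the period from which values are drawn, and on that reading the two sections are compatible. The article is condensed, and time coding, visit windows and covariance structure are usually left to the analysis plan, which is not shown.

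Much of this stands. The missing windows or covariance details are not a fault in themselves, and there is no flat contradiction. What remains is that the article does state what the model estimates, and that statement does not target the 24-month change. A wording that allows two different primary estimates needs to be settled.

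Three further replies are fair:

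- No section says that visit timing differs between arms, and recruitment ran through scheduled well-child visits. A reader might infer that timing bias is present, but the documents show only that the described comparison would not guard against it. Intervention children enter by referral and controls by having a well-child visit, so equal timing is not assured either.
- Children with many visits do not dominate. With one baseline value and a child intercept, the variance of a child's contrast is proportional to 1 + 1/k for k follow-up values, so frequent attenders carry at most about twice the weight of a child with one value.
- A random slope is a modelling preference. Its absence is not an error.

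**Conclusion.** The point holds as a mismatch of target. The primary outcome is a 24-month change, and the stated estimate is an average with no time point. Read as written, it depends on visit timing and can include values beyond 24 months.

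Its size is conditional. Under linear build-up the average is 75% of the 24-month effect with visits at 12 and 24 months, and 62.5% with visits at 6, 12, 18 and 24. It equals the 24-month effect when all visits fall after an early plateau, and exceeds it if the effect fades. The spurious difference of −0.50 units under unequal timing rests on an assumed drift and assumed schedules.

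Two stronger conclusions may tempt a reader, and the documents support neither. One is that the planned estimate will be too small. That follows only if the effect accrues gradually, which is plausible with coaching over 24 months but is not stated. The other is that an attenuated 5.3 would fall below what the trial can detect. That treats 5.3 as a 24-month value, which the Power section does not say. It also holds the standard error fixed, although averaging several values per child reduces it.

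**What to change.** Reword the planned analysis before outcomes are analysed:

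- Use all BMI values up to 24 months, plus a pre-specified window around that point. The window must fit the analysis date: a child who enters in December 2024 reaches 30 months in June 2027, after the results are due, so a window running to 30 months would be cut short for late entrants.
- Model time since baseline, either continuous or in windows, with arm-by-time terms.
- Name the model-based arm contrast in change at 24 months as the primary estimate.
- Report the time-averaged difference-in-difference as secondary. A child random slope can be a sensitivity analysis.

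The cost is wording and code, with no new data collection, and some precision. As a guide, take four follow-up values under a child-intercept model. The within-child variance is proportional to 1.25 for the pooled average and to 2 for a contrast at one categorical time, so that part of the standard error rises by a factor of √(2/1.25) = 1.26. A linear time term loses less, but relies on the linear shape.

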## Methods

### Study Design

The WC4K trial is a cluster randomized pragmatic trial with a parallel design, evaluating the effectiveness and sustainability of an MI-based behavioral health intervention integrated into pediatric primary care. Clinics were the unit of randomization. This study was guided by the Pragmatic-Explanatory Continuum Indicator Summary tool [41,42], with scores of 4 or 5 across all 9 domains indicating a highly pragmatic approach.

The WC4K program uses MI to promote healthy lifestyle changes aimed at reducing excess weight in children with overweight or obesity. Key behavioral targets include fruit and vegetable intake, consumption of sugar-sweetened beverages, physical activity, and screen time. The intervention is a modified version of the Brief Motivational Interviewing to Reduce BMI (BMI^2^) intervention [40]. This study uses an implementation-effectiveness hybrid design (type 2) to allow a simultaneous evaluation of clinical outcomes and implementation processes [43].

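### As specified, the primary mixed model names only a child random intercept and omits between-clinic variation in change, although clinics were randomized; at the plan's own inputs the nominal 5% test would have an error rate of about 28%

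*Protocol article*

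**What the plan says.** All places are in the Protocol article.

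- **Study Design:** "Clinics were the unit of randomization".
- **Power:** the calculation is for the difference in change in BMI distance and "takes into account the intraclass correlation among children within clinics". Its inputs include "an intraclass correlation of 0.01" and "a coefficient of variation of 0.9, and an SD of 27.0% for change in BMI distance".
- **Planned Statistical Analysis:** the effect is a difference in difference from repeated BMI measurements. A linear mixed model is introduced as the means of dealing with clustering, without naming the level. The next sentence gives the one random effect: "The model will include a random intercept for “child” to account for repeated measures". Unbalanced baseline covariates and site-level characteristics are added as fixed effects.

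The section names no clinic random effect, clinic-by-time effect, clinic-level robust variance or clinic-based degrees of freedom. Separately, Identification of the Control Cohort says that control children will be weighted by inverse propensity scores.

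**The concern.** A child intercept absorbs the correlation between measurements of one child. It does nothing for the correlation between different children of one clinic. When clinics are randomized, the second correlation sets the precision of the treatment effect. Fixed site-level characteristics remove only the part of the clinic variation that they explain.

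If the model is run as written, children of one clinic count as independent evidence. Standard errors are then too small, confidence intervals too narrow, and the primary test rejects a true null more often than 5%. The analysis would also fail to deliver the allowance for clinics on which the sample size was built.

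**Working it through.** **Inputs, all from the Power section.** "With 24 clinics in the intervention arm and 26 in the control arm"; about 3300 children per arm; "assuming a 2-sided α of .05"; ICC 0.01; coefficient of variation (CV) of clinic size 0.9; SD of change 27.0.

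**Assumption.** The ICC of 0.01 is that of each child's change. The article does not say so outright, but the power outcome is a difference in change and the ICC stands in one sentence with the SD of change.

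**1. Design effect with unequal clinics.** DE = 1 + [(1 + CV²)m − 1] × ICC, where m is the mean number of children per clinic.

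- Intervention: m = 3300/24 = 137.5; DE = 1 + (1.81 × 137.5 − 1) × 0.01 = 3.48.
- Control: m = 3300/26 = 126.9; DE = 1 + (1.81 × 126.9 − 1) × 0.01 = 3.29.
- Mean DE = 3.38, so the effective size is 3300/3.38, about 975 per arm.

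**2. The plan's own figure.** The section claims adequate power for a difference of 1 to 5 units but gives no power value, so there is no number to reproduce. With clinics allowed for, SE = 27 × √(2 × 3.383/3300) = 1.22. The difference detectable with 80% power is (1.96 + 0.84) × 1.22, about 3.4 units. Without clinics, SE = 27 × √(2/3300) = 0.66.

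**3. Error rate when clinic is omitted.** The ratio of true to reported SE is √3.383 = 1.84. The true size of the nominal 5% test is 2 × [1 − Φ(1.96/1.839)] = 28.7%. With 25 control clinics, the number in the Results text, it is 29.0%.

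**4. Simulation.** In 10,000 simulated null trials (24 and 26 clinics, gamma-distributed clinic sizes, ICC 0.01 on change), the test that omits clinic rejected in 27.7%. A test that included the between-clinic variance of change, with variance components treated as known, rejected in 4.7%.

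**5. Sensitivity** (formula; the ICC 0.001, 0.005 and 0.02 rows use about 132 children per clinic):

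| ICC of change | CV | True size of the 5% test |
|---|---|---|
| 0.001 | 0.9 | 7.8% |
| 0.005 | 0.9 | 18.5% |
| 0.01 | 0 (equal clinics) | 19.7% (simulated 19.6%) |
| 0.01 | 0.9 | 28.7% (simulated 27.7%) |
| 0.02 | 0.9 | 41% |

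**6. Does the child intercept help?** In a constructed data set with one baseline and one follow-up value per child, the child-intercept model gave an SE of 1.339 for the arm-by-time effect. A plain comparison of change scores that ignores clinic also gave 1.339. The clinic-level robust SE was 2.261. That data set used a larger clinic effect than the plan assumes, so only the equality of the first two figures carries over.

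**7. Would a clinic intercept be enough?** Suppose a child's value contains a constant clinic term b, a clinic-specific change c that acts at follow-up only, a child term a, and measurement error. Follow-up minus baseline then leaves c and the errors; a and b cancel. An intercept for clinic models b, but c is what inflates the variance of the difference in difference.

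**The case against.** The sentence just before the quoted one says that the mixed model serves to deal with clustering. In a trial that randomizes clinics, this most naturally means clinics, and naming one random effect does not say that there are no others. This is a condensed article, and degrees-of-freedom methods and small-sample corrections commonly wait for the statistical analysis plan, which is not shown.

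Much of this stands. A reader might infer that the trial will ignore clinic altogether, or that the analysis and the power calculation have opposite aims. The documents do not support either: the stated intent is the same in both sections. What remains is that the article does not leave the random-effects structure open. It states one, and the term it states cannot meet that intent at the level that was randomized.

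A reader might also take 28% as the trial's actual error rate, or as a result of the ICC alone. It is neither. It needs the ICC to apply to change, since clinic variation that is constant over time drops out. It also needs the CV of 0.9, which the Power section first gives for all children with overweight or obesity per site, not for those analysed. Propensity weights could change the effective clinic sizes, and site covariates could absorb some clinic variation; neither was modelled. The calculation also treats each child as having one change score, whereas the plan uses all available BMI values.

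**Conclusion.** The point holds for the model as specified: between-clinic variation in change is missing from the primary analysis, although clinics were randomized and the power section allows for correlation within them. At ICC 0.01 on change, CV 0.9 and 3300 children per arm, the nominal 5% test has a true size of about 28%. Under the alternatives tried it ranges from about 8% to 41%; even the most favourable exceeds 5%. These figures are conditional on the assumptions above and come before weighting and site covariates. If the full analysis plan already names a suitable clinic term, the test itself is sound, and the article's description of the primary model is what needs correcting. Because validity of the primary test is at stake, this should be settled before the outcome analysis.

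**What to change.** State in Planned Statistical Analysis that the primary arm-by-time effect will be estimated with clinic-level variation in change accounted for. Two routes would do this:

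- **Preferred:** the propensity-weighted model with clinic-level cluster-robust variance and a small-sample correction. It accommodates the weights described under Identification of the Control Cohort.
- **Alternative:** random effects for child, clinic and clinic-by-time, with Kenward-Roger or Satterthwaite degrees of freedom. The text must then also say how the weights enter.

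In either case, degrees of freedom should rest on the number of clinics: about 47 to 48 (49 or 50 clinics less 2). Adding a clinic random intercept alone would not repair the test.

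The cost is wording and code. Intervals become wider, by a factor of about 1.84 at the plan's inputs, but the power section already assumes that loss of precision.

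### The only term named for repeated BMI readings is a child random intercept; unless more is added, the standard error of the difference-in-differences is too small when children grow at different rates and have two or more follow-up readings

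*Protocol article*

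**What the plan says.** The primary outcome is defined under Outcome Measures: "The primary outcome is a change in BMI-for-age over 24 months". Readings come from routine care: "No additional visits were scheduled for height and weight collection". Their number and timing will therefore differ between children, and the article gives no count.

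Under Planned Statistical Analysis, "the DID model will estimate the average within-child change from baseline to follow-up", "using all available BMI data points". A linear mixed model is chosen to handle clustering, and the one random effect named is this: "The model will include a random intercept for “child” to account for repeated measures". No random slope, residual correlation, clinic effect or type of standard error is named, and none is ruled out.

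The Power section is "assuming a 2-sided α of .05, an intraclass correlation of 0.01, a coefficient of variation of 0.9", together with "an SD of 27.0% for change in BMI distance". A second SD, 14.7, is attached to the expected effect size of 5.3; the text does not say that it is an SD of change.

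**The concern.** A random intercept with independent residuals is compound symmetry. The SD of the difference between two readings of one child is then the same at one month as at 24 months. Children aged 3 to 8 followed for two years are likely to drift apart, because each has an own growth rate. All follow-up readings of a child share that rate, so averaging them does not remove its variation. The model treats it as independent noise that does average out.

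If so, the confidence interval for the primary contrast is too narrow and the test rejects a true null more often than the 5% used in the Power section. The problem grows with the number of follow-up readings. A clinic random intercept would not help: it is constant over time and cancels from the within-child change.

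**Working it through.** **Inputs from the article:** two-sided α 0.05; SD of change 27.0; the second SD, 14.7, used here as an alternative SD of change; 24-month follow-up; all readings used; contrast read as mean follow-up minus baseline.

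**Assumptions not in the article:** K equally spaced follow-ups, the last at 24 months; visit-to-visit noise SD e; a linear random slope with variance s² (time scaled to 0–1); no clinic effect; no weighting.

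**Step 1. What equal correlation implies.** The SD of a difference is √2 × residual SD, so the residual SD is 27.0/√2 = 19.1 (or 14.7/√2 = 10.4). Two readings a month apart would differ with an SD of 27.0 (or 14.7) points. For a child 35% above the median, the middle of the Power section's 30% to 40%, that is 27.0/135 = 20% of BMI (or 14.7/135 = 11%).

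**Step 2. Formulas.**
- s² = SD² − 2e², so that the 24-month change has the chosen SD.
- True variance of (mean of K follow-ups − baseline) = s²·t̄² + e²(1 + 1/K), with t̄ the mean follow-up time.
- Model variance = (s²·V + e²)(1 + 1/K), with V the sample variance (divisor K) of the K + 1 times including baseline.
- Size = 2[1 − Φ(1.96 × R)], with R = √(model variance / true variance).

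**Step 3. Nominal level.** The only figure to reproduce is the 5%. For K = 1, t̄ = 1 and V = 0.5, so both variances equal s² + 2e², R = 1 and the size is 5.0%.

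**Step 4. SD 14.7, e = 4**, so s² = 216.09 − 32 = 184.09.

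| K | t̄ | V | True variance | Model variance | R | Size |
|---|---|---|---|---|---|---|
| 2 | 0.75 | 0.25 | 103.6 + 24 = 127.6 | 62.0 × 1.5 = 93.0 | 0.85 | 9.4% |
| 4 | 0.625 | 0.156 | 71.9 + 20 = 91.9 | 44.8 × 1.25 = 56.0 | 0.78 | 12.6% |
| 8 | 0.5625 | 0.117 | 58.2 + 18 = 76.2 | 37.6 × 1.125 = 42.3 | 0.74 | 14.4% |

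**Step 5. Size over the assumed grid.**

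| SD of change | e | K = 2 | K = 4 | K = 8 |
|---|---|---|---|---|
| 14.7 | 2 | 10.5% | 15.4% | 18.7% |
| 14.7 | 6 | 8.0% | 9.6% | 10.3% |
| 14.7 | 8 | 6.5% | 7.1% | 7.3% |
| 14.7 | 10 | 5.2% | 5.3% | 5.3% |
| 27.0 | 2 | 10.8% | 16.2% | 20.0% |
| 27.0 | 6 | 9.9% | 13.7% | 16.1% |
| 27.0 | 10 | 8.4% | 10.4% | 11.4% |

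The inflation vanishes as e approaches 10.4 with SD 14.7, as Step 1 predicts.

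**Step 6. Other true structures.** A correlation that decays with time, in place of slopes, gives 6.6% to 12.1%. Simulation with irregular visits (2 to 6 follow-ups on average, slope SD 2 to 6.8 points per year, e of 3 or 4) gives 5.3% to 13.7%.

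**Step 7. Which standard error cures it.** Simulated size with four irregular follow-ups on average, slope SD 6.8 per year and e = 4:

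| Setting | Child intercept, model-based | Robust, by child | Robust, by clinic |
|---|---|---|---|
| No clinic effect, 1,000 per arm | 10.4% | 4.0% | 4.1% |
| Clinics vary in slope, intraclass correlation 0.01, 3,300 per arm | 25.5% | 12.8% | 3.5% |

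The second row uses 400 runs and clinics of roughly equal size, and applies the article's 0.01 to change.

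**The case against.** The strongest objection is that the article does not say the child intercept is the only covariance term. It is a condensed account, and slopes, residual structure, time coding and type of standard error are commonly left to an analysis plan, which is not shown here. This stands: that the intercept is used alone is an inference. But the article did choose a structure and state its purpose, and that structure fits poorly with its own SD of change. This is therefore a comment on a stated choice and not a complaint about missing detail.

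The magnitude is also conditional. Readings per child, their spacing and the noise SD are all assumed, and it is not shown that most children will have two or more follow-ups. The planned inverse probability weighting is not in the calculation. If robust standard errors accompany it, the child-level problem goes away, and if they are clustered on clinic, so does the clinic-level one.

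A reader might infer that the test will reject 10% to 15% of the time. The article does not support that; it is one slice of the range. A reader might also cite the larger errors of an arm-by-time slope test (11% to 48% for noise SDs of 2 to 6). Planned Statistical Analysis describes an average change from baseline to follow-up and no such slope test.

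**Conclusion.** The point holds in conditional form. Unless further terms or robust standard errors are used, the stated model understates the standard error of the primary contrast when children differ in growth rate and have two or more follow-ups. Under the assumed inputs the true size is about 5% to 20%; with a single follow-up at a fixed time it is 5%. The figure for equal correlation rests most firmly on 27.0, the only value labelled an SD of change; the 14.7 rows hold only if that value is one too.

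It would be too strong to call the child covariance, taken by itself, a fatal flaw. Where clinics vary, repairing only the child level still leaves a simulated size of about 13%, against about 4% with clinic-clustered errors. The clinic-level standard error is the part that matters most.

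**What to change.** In Planned Statistical Analysis, replace the sentence on the child random intercept with wording such as:

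> The model will have a child-level random intercept and a correlated child-level random slope for time since baseline. Inference will use robust standard errors clustered on clinic, the unit of randomization, with a small-sample correction for the number of clinics.

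A serial or unstructured residual covariance over visit windows could replace the random slope. If the slope model does not converge, the clinic-clustered standard error suffices by itself with the child intercept kept. A child slope or child-level robust error alone would not cover clinic variation. If the analysis plan already contains such a standard error, one clause saying so closes the point.

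The cost is a sentence or two, no new data and somewhat wider intervals. For the same estimator, the child-level part of the interval widens by 1/R: 1.17 to 1.34 times in Step 4, and about 1.01 to 1.53 times over the grid (R from 0.99 to 0.654). Any clinic variation adds to that.
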